#### Data Management

All data gathered by questionnaires will be digitalized for further processing. Functional testing will be controlled via Unity3D (Unity Technologies, San Francisco, United States), which also assigns basic demographic data to the measurement data of each participant. All functional measurements will be streamed and synchronized using the LabStreamingLayer (Swartz Center for Computational Neuroscience, UCSD, US). Synchronized data streams will comprise gait analyses (OptoGait, Microgate, Bolzano, IT), EEG recording (LiveAMP, Brain Products, Gilching, DE), kinematics (VivePro, HTC, Taoyuan, TW), and secondary task performance (VivePro, HTC, Taoyuan, TW & Raspberry Pi, Raspberry Pi Foundation, Cambridge, GB).

Data processing and feature extraction will be done using customized MATLAB scripts (The MathWorks, Inc.), EEGLAB (Delorme and Makeig, 2004). After importing all synchronized Motion Capture and EEG data streams, we will preprocess the EEG data using the bemobil-pipeline.^1^ This pipeline comprises filtering, data cleaning (channel and line noise), independent component analysis computation and equivalent dipole modeling for activity sources. Gait data will be analyzed separately as well as events will be extracted which in turn will be used in joint analyses like gait-phase-related brain activity changes. Following processing of the event-related potentials or spectral measures will be done with respective processing pipelines like the unfold-toolbox (Ehinger and Dimigen, 2019). Source-based analysis will apply repetitive k-means clustering to ensure a stable clustering solution for further analysis of clusters representing the brain regions of interest and connectivity measures.

#### Statistical Analysis

Descriptive data will be presented as mean (*M*) and standard deviation (*SD*). Normal distribution and homoscedasticity will be checked by the Shapiro-Wilk-Test and the Levene-Test, respectively. Dual-task costs will be analyzed using univariate analyses of variances (ANOVA) including the between-subject factors *age* (younger vs. older) and in case of older *hearing ability* (hearing impaired vs. non-hearing impaired) and the within-subject factors *task complexity* (single- vs. dual-task) and *stimulus modality* (visual vs. auditory).

Significance will be set at α = 0.05. The effect size will be presented as partial eta squared. In all *post hoc* comparisons we will control for multiple comparisons (e.g., Bonferroni). Statistical analyses will be done by using SPSS (IBM, SPSS Inc., Chicago, IL, United States) or R (R Core Team, 2013).

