Researchers have attempted to explain the association between hearing impairment and mobility decline in terms of competition for limited shared cognitive resources (Bruce et al., 2019). In everyday life, balancing or walking is rarely the only task performed at a time (single-task) and it is mostly performed together with another task (dual-task) or sometimes even as a multitasking activity (Faulkner et al., 2007). Cognitive-motor dual-task (CMDT) studies usually compare a single-task condition, such as a postural or walking task, with a dual-task condition, which combines the same motor task with a synchronous cognitive task. By comparing performance in both conditions, we can then calculate dual-task costs (DTCs: single-task minus dual-task performance divided by single-task performance) which indicate the degree of performance decline in one or both tasks due to limited cognitive capacity (Li and Lindenberger, 2002; Marusic et al., 2015; Janouch et al., 2018; Wollesen et al., 2018). CMDT studies have shown that as cognitive load increases during the manipulation of sensory information, older adults show greater postural performance decrements compared to their younger counterparts (Redfern et al., 2001; Doumas et al., 2008). Competition for cognitive capacity is also observed when auditory challenges are experimentally imposed on different motor tasks, such as balancing or walking (Nieborowska et al., 2019), or when older adults with hearing impairment undergo CMDT (Lau et al., 2016). The so-called “posture-first” hypothesis or strategy (Shumway-Cook et al., 1997) describes the prioritization of physical safety by allocating more attention to motor performance than to cognitive performance. In older adults, such prioritization increases with task complexity, postural threat, or fear of falling (Li et al., 2001).

Since older adults often exhibit hearing impairments that severely affect their lives, investigating the interaction between age-related hearing impairment and decline in other domains (e.g., vision, cognition, and mobility) at the behavioral and neurophysiological levels could elucidate the underlying mechanisms. In addition, this research could lead to therapeutically promising insights by providing a better understanding of the risk of falls leading toward improved fall prevention programs.

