Previous research on cognitive-motor interference (CMI) while dual-task walking showed that spatio-temporal gait parameters like walking speed, step length, and arm swing symmetry are affected by the secondary task (Mirelman et al., 2015; Killeen et al., 2017). Moreover, there is evidence that different pre-conditions of the individuals’ cognitive-motor abilities, such as balance decline, concern about falling, and hearing impairments, negatively influence dual-task walking, that is reduced walking speed, step length, heel-strike, and foot-rolling movements (Wollesen et al., 2017a,b). These effects were maintained after controlling for age and comorbidities and showed that older adults with concerns about falling or hearing impairment have worse initial conditions on their gait quality and therefore have an increased risk of falling. More research is warranted to confirm these findings, as they relied purely on behavioral data with biomechanical walking measurements and cognitive performance through error counting or reaction times. Therefore, it is relevant to investigate the interaction between the motor and the cognitive system by analyzing the processes and conditions that influence older adults’ gait performance in situations that require concurrent performance of sensorimotor and cognitive tasks.

The following experiment will use walking tasks with different complexities and priorities, and record behavioral (spatio-temporal gait parameters) as well as neurophysiological data.

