### Aims and Research Questions for the Study

The present study is designed to investigate the following three foci using a MoBI approach:

Focus 1: General characteristics of dual-task walking of all participants.

•How does cognitive task performance differ when using visual or auditory stimuli in single- and dual-task conditions?•How are dual-task costs represented in gait parameters?•How are neuronal correlates of auditory and visual information processing impacted by dual-task interference during walking?

Focus 2: Age-related differences in dual-task walking.

•Can we replicate the age-related increase in dual-task costs?•How are the age-related differences in performance reflected in the respective brain activity of younger and older adults?•How do younger and older adults differ in their gait parameters and gait-phase related stimuli processing?

Focus 3: Differences of hearing-impaired and healthy older participants in dual-task walking.

•How do auditory vs. visual information processing and movement control vary with regards to the effect of hearing impairment represented in both cognitive task stimuli modalities and dual-task vs. single-task performance?•How are dual-task costs reflected in biomechanical and neuropsychological measures of hearing-impaired participants?

The overall hypothesis is that there are differences in dual-task costs and their corresponding neuronal correlates between the three groups with the highest disadvantages for the group of older adults with impaired hearing. We hypothesize that the performance differences are linked to the different cognitive-motor processes; i.e., information or stimulus input, resource allocation, and movement execution. Further, we hypothesize that the increasing task complexity (from single-task to dual-task), as well as the stimulus modality (visual vs. auditory), will further diminish the walking performance and increase neuronal activity.

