#### Primary Outcomes

The primary outcome of the present study will be the dual-task cost occurring in over-ground walking with a cognitive secondary task. Gait parameters will be recorded for single and dual task walking, EEG measures will be conducted throughout the entire experiment (ST cognitive; ST walking; DT walking).

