Starting with the general characteristics of dual-task walking for all participants this study will compare the influence of visual or auditory secondary stimuli while walking. One might expect that with respect to age comparison the behavioral data might be different and that older adults show more changes in the observed gait parameters (e.g., speed, step length, double support time; refs). Because the walking performance between younger and older adults already differs at ST walking (Neider et al., 2011; Klotzbier et al., 2021), we expect especially the DT situation with additional visual input to lead to the highest performance decrements (for an overview cf. Beurskens and Bock, 2012). Additionally, there is first evidence that older and younger adults might show DT-related differences in walking patterns related to pace (like walking speed) or rhythm (like cadence or double support time; Beauchet et al., 2019; Klotzbier et al., 2021). The study by Klotzbier et al. (2021) showed that younger adults’ gait performance during a verbal fluency DT (naming animals) only led to reduced walking speed, whereas for the older adults both elements of pace and rhythm were affected (Klotzbier et al., 2021). It is of interest if these results could be replicated for the integrated visual and auditory tasks within this study. Moreover, we expect first insights into the neuronal correlates of the interaction of the secondary task and the two dimensions of gait performance (parameters of rhythm vs. parameters of pace and effects on arm swing as well as hip rotation) as well as the different phases of a gait cycle (gait initiation, swing phases as well as double support phase; for example as shown for persons with Parkinson’s disease; Fino et al., 2018).

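### The protocol's only formula for dual-task cost is proportional, but the ANOVA named for dual-task costs tests a group-by-task interaction, additive unless performance is transformed, and the two can differ on age

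*Protocol article*

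**What the plan says.** The Introduction of the protocol article defines dual-task cost as "single-task minus dual-task performance divided by single-task performance". No other section gives a formula. Primary Outcomes uses the same term without defining it again: "The primary outcome of the present study will be the dual-task cost occurring in over-ground walking with a cognitive secondary task".

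Statistical Analysis states: "Dual-task costs will be analyzed using univariate analyses of variances (ANOVA) including the between-subject factors" age and, among older adults, hearing ability. The same sentence lists the "within-subject factors *task complexity* (single- vs. dual-task") and stimulus modality. No transformation is mentioned. Sample Size Estimate/Power Calculations names a repeated-measures F test of a within-between interaction.

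On group differences at single task, the Discussion says that "the walking performance between younger and older adults already differs at ST walking". For hearing, the Introduction says only that "older adults with concerns about falling or hearing impairment have worse initial conditions on their gait quality". Focus 2 of the aims asks: "Can we replicate the age-related increase in dual-task costs".

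**The concern.** A score of the form (single − dual)/single uses up both task conditions. It cannot then be crossed with a factor whose levels are single and dual. Either the dependent variable is the proportional score and the task factor does not belong, or the dependent variable is performance and the model does not test the endpoint as the Introduction defines it.

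Only the second reading gives a model that can be run. The group difference in cost is then the group-by-task interaction, and without a transformation that is a difference of differences in measured units.

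The two quantities are different estimands. Their tests can part company when groups start from different single-task levels, which the protocol itself expects for age in walking. The answer to the Focus 2 replication question could then depend on which scale is reported, and that choice could be made after the results are known.

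**Working it through.** **Does the stated model fit the stated score?** Let S be single-task and D dual-task performance.
- Introduction: cost = (S − D)/S, one value per person and modality, with no task level left.
- Statistical Analysis: task, with levels S and D, is a within-subject factor. The dependent variable must therefore be S and D themselves.
- Untransformed, the group-by-task term compares the mean of S − D between groups.

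**When do the scales differ?** Write c for the proportional cost, Y for young and O for older. At group-mean level the raw cost is c × S, so

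raw difference (O − Y) = c_O × S_O − c_Y × S_Y.

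If c_O = c_Y = c, this equals c × (S_O − S_Y). It is zero when the single-task means are equal or the cost is zero, and non-zero otherwise.

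**Gait speed, assumed values.** The documents give no speeds. Take S_Y = 1.40 and S_O = 1.20 m/s.
- Equal 10% cost: raw costs are 0.10 × 1.40 = 0.14 and 0.10 × 1.20 = 0.12 m/s. The raw difference is 0.12 − 0.14 = −0.02 m/s, a larger cost in the young.
- Equal raw cost of 0.14 m/s: proportional costs are 0.14/1.40 = 10.0% and 0.14/1.20 = 11.7%.
- So, with 10% in the young, an older-group cost above 10% but below 11.7% is a true proportional increase that appears as a decrease on the raw scale.

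**How often would this matter?** Assume a single-task SD of 0.15 m/s, a proportional cost of 10% with SD 5 points in both groups, and a two-sided t test at 0.05.
- Variance of the raw cost = S² × 0.05² + 0.10² × 0.15² + 0.15² × 0.05².
- Young: 0.00490 + 0.000225 + 0.000056 = 0.00518. Older: 0.00360 + 0.000225 + 0.000056 = 0.00388.
- Standard error at 36 per group: √((0.00518 + 0.00388)/36) = 0.0159. Then 0.02/0.0159 = 1.26, and P(Z > 1.96 − 1.26) ≈ 24%.
- Standard error at 48 per group: √(0.00906/48) = 0.0137. Then 0.02/0.0137 = 1.46, and P(Z > 0.50) ≈ 31%.
- Simulation (4,000 trials per setting) gives about 24–30% over 36 to 48 per group. The proportional and log-scale tests stay near 5%.

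A second noise model (cost 10%, additive noise SD 0.06 m/s, 36 per group, 5,000 trials) shows the effect in both directions. Entries are rejection rates.

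| Assumed older single-task speed (young 1.40 m/s) | Equal proportional cost: raw test | Equal raw cost: proportional test |
|---|---|---|
| 1.40 | 4% | 5% |
| 1.30 | 10% | 11% |
| 1.20 | 26% | 31% |
| 1.10 | 53% | 63% |

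In each column the test that matches the true equality stays near 5%. Disagreement grows with the single-task gap, and neither scale is shown to be the wrong one.

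**Does a log scale bring the model into line?** log D − log S = log(1 − c), so the group-by-task term is log[(1 − c_O)/(1 − c_Y)], which is zero when the proportional costs are equal. It approximates the Introduction's cost: for c = 0.10, −log(0.90) = 0.105.

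**The case against.** The formula stands in the Introduction, in a description of what dual-task studies usually do. The Methods never formally adopt it. Trial Design, Data Collection, Statistical Analysis and the sample-size section all treat cost as a contrast between conditions and agree among themselves. This stands as a limit: the conflict is between one background definition and the Methods. It does not remove the point, because that is the only formula given and the primary outcome uses the same term.

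A reader might infer that the plan commits to raw m/s or ms. It does not say so. The additive scale follows from the task factor with no transformation stated, and a task factor would also suit log-transformed performance. An unshown analysis plan could settle the transformation, but the article prints both a formula and a model, and they do not match.

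A reader might also infer that the analysis would manufacture an age effect in response time. With assumed single-task means of 450 and 570 ms and an equal 15% cost, the raw interaction is 0.15 × 120 = 18 ms. Simulated rejection is then 29–63% at 36 per group and 37–76% at 48, depending on the assumed spread of cost. No section states that older adults are slower at single-task response time, so these figures are conditional and cannot be the main evidence.

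For gait speed the distortion runs against the hypothesis. If older adults walk more slowly at single task, a larger raw cost in them implies a larger proportional cost at group-mean level. A positive raw-scale result would therefore generally hold on both scales.

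Finally, it would be too strong to say that the scales agree only when single-task levels are equal. Conclusions also agree when cost is near zero or the true group difference is large.

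**Conclusion.** The point holds: the model named for dual-task costs does not test dual-task cost as the protocol's only formula defines it, and no section reconciles the two. For age and gait the protocol supplies the condition under which the scales can diverge. For hearing the support is qualitative only.

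The size is illustrative. At an assumed 1.40 versus 1.20 m/s and an equal 10% cost, the additive interaction is 0.02 m/s in the direction opposite to the expected age effect, significant in about 24–30% of trials. The consequence for gait speed is a missed or reversed age effect, not a spurious increase. Response time could be biased the other way if older adults are slower at single task, which the documents do not state. The documents do not show that either scale is wrong in itself; the defect is that formula and model differ on the primary outcome. It should be corrected before analysis.

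**What to change.** State the cost formula in Primary Outcomes and make the gait analysis match it, in one of two ways:
- Analyse the per-person proportional cost by group and modality, with no task factor.
- Keep the task factor and analyse log-transformed positive measures (walking speed, step length, response time). The group-by-task term is then a ratio of proportional changes that approximates the Introduction's cost.

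Report the raw-unit interaction as secondary. State the scale separately for accuracy and for EEG amplitudes: logs do not apply directly there, since amplitudes can be negative and accuracy needs its own choice.

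No new data are needed. Effects would be reported as percentages rather than in m/s or ms. If the per-person cost is chosen, the task factor disappears and the within-between interaction named in the sample-size section must be restated to match.

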#### Single-Task Walking With Response Device

Single-task walking will take place as one of five conditions in pseudo-randomized order. Participants will walk constantly 520 m (400 m within the OptoGait), but with the response devices in their hands. Participants will be able to choose their preferred walking speed and turn around by walking around a cone placed at least 1 m from the ends of the OptoGait gangway. From the single-task walking, we will also extract the distance walked within the first 6 min as a slightly modified measure of the 6-min walk test (ATS Committee on Proficiency Standards for Clinical Pulmonary Function Laboratories, 2002).

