#### Cognitive Tasks While Sitting—Single-Task-Conditions

Participants will be asked to perform cognitive tasks (stimulus-discrimination). During these tasks, participants will be wearing the EEG-system, a custom-made spectacle frame with two LEDs attached to present light stimuli in the peripheral visual field. In addition, participants will wear headphones for presenting auditory stimuli. While sitting in the middle of the OptoGait and performing the task, participants will be asked to look in a walking direction. 200 stimuli (in either the visual or the auditory condition) will be presented with a varying inter-stimulus interval (400–800 ms) and a duration of 100 ms. Participants will be asked to react within a time window of 900 ms to the stimuli by pressing a button on the Vive controller in the respective hand. Thus, the maximal trial duration will vary between 1.4–1.8 s. The participant’s response will initiate the next trial and in case no response is given within the required time window, the next trial will start after 900 ms.

Visual task: Visual light stimuli, magenta (red and blue LED) and/or cyan (green and blue LED) flashes, will be presented counterbalanced and pseudo-randomized on the left or right side of the spectacle frame. Participants will have to which color (magenta or cyan) was presented (color discrimination task) with a right/left hand button press.

Auditory task: Auditory stimuli (high and low tone of 1000 and 500 Hz) will be presented for the duration of 100 ms either binaurally or to the left or right side with a volume of 50–60 dB (equals volume of an indoor conversation, Pearsons et al., 1977), regardless of presence and severity of the hearing impairment. Participants will have to indicate which pitch (low or high) was presented (pitch discrimination task) with a right/left hand button press.

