#### Cognitive Tasks While Walking—Dual-Task-Conditions

For the dual-task conditions, a walking time of 6–7.5 min is estimated for each condition, including turnarounds at the end of the gangway. The same visual and auditory stimuli as described in the previous section will be used. Participants will be asked to simultaneously walk up and down the OptoGait gangway. Participants will be able to choose their preferred walking speed and turn around by walking around a cone, placed at least 1 m from the ends of the OptoGait gangway. Five stimuli will be presented each time participants walk the 10 m gangway of the OptoGait. Each task will end after the participants walked 520 m (400 m within the OptoGait) and 200 presented stimuli.

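### The single ANOVA stated for dual-task costs crosses single/dual task with modality, a crossing that neither the gait dual-task cost (the primary outcome) nor raw gait can supply

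*Protocol article*

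**What the plan says.** The protocol article, under Primary Outcomes, states: "The primary outcome of the present study will be the dual-task cost occurring in over-ground walking with a cognitive secondary task". The Introduction defines the cost as "single-task minus dual-task performance divided by single-task performance".

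Under Statistical Analysis, one model is given: "Dual-task costs will be analyzed using univariate analyses of variances (ANOVA) including the between-subject factors" age and, among older participants, hearing ability. Its within-subject factors are task complexity and modality ("single- vs. dual-task) and *stimulus modality* (visual vs. auditory").

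The conditions are described in three places:
- Walking alone: "Single-task walking will take place as one of five conditions in pseudo-randomized order". Participants hold the response devices, and no stimulus task is described.
- Sitting, cognitive task only: "200 stimuli (in either the visual or the auditory condition) will be presented".
- Walking with a cognitive task: "The same visual and auditory stimuli as described in the previous section will be used".

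The Trial Design section lists task condition and modality as design factors and allows cost analyses to address either gait or cognitive performance. The Data Collection section says that comparing conditions within participants is how dual-task costs will be studied.

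**The concern.** A model that names an outcome and its factors should have data in every cell that those factors create. Here the outcome named is a cost, and a cost is itself a comparison of single with dual task. Putting single versus dual task into the model as a factor asks for a single-task value of a quantity that has none.

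The natural repair is to analyse raw gait instead. It meets a second obstacle: walking alone has no visual and auditory version, so task complexity and modality are not fully crossed for gait.

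This is the only model given for the primary outcome. An analyst would have to depart from it, and the possible departures are not equivalent. The terms affected are those involving modality, including the expectation in the Discussion that hearing-impaired older adults do worst in the auditory condition.

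**Working it through.** The plan gives no figure to reproduce on this point. The check is a count of cells.

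**Inputs.** The cost formula (Introduction). The five conditions: 1 single-task walk + 2 sitting tasks + 2 dual-task walks = 5, which agrees with the number stated in the single-task walking section. The baseline section adds a 3-minute walk without the response device; it has no stimulus modality either. The model's within-subject factors have two levels each, so they need 2 × 2 = 4 cells.

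**Cells available per participant**

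| Outcome | Single, visual | Single, auditory | Dual, visual | Dual, auditory | Cells |
|---|---|---|---|---|---|
| Dual-task cost (ratio) | none | none | yes | yes | 2 of 4 |
| Raw gait | one walk, no modality | same walk | yes | yes | 3 of 4 |
| Raw cognitive performance | yes | yes | yes | yes | 4 of 4 |

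**Rank of the design.** Code task t as −1 (single) or +1 (dual), and modality m as +1 (visual), −1 (auditory) or 0 (no modality). The columns are intercept, t, m and t×m.
- Cost: rows (1, 1, 1, 1) and (1, 1, −1, −1). The rank is 2. The t column equals the intercept, and t×m equals m. Only modality can be a within-subject factor.
- Raw gait: rows (1, −1, 0, 0), (1, 1, 1, 1) and (1, 1, −1, −1). The rank is 3, and t×m equals m. No other coding helps, because three distinct rows cannot give rank 4.
- Raw cognitive performance: rows (1, −1, 1, −1), (1, −1, −1, 1), (1, 1, 1, 1) and (1, 1, −1, −1). The rank is 4, so the full crossing is estimable. Stimulus-locked EEG has the same four cells.

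**If the single-task walk were entered twice.** Let ST be the single-task walk, and DTv and DTa the visual and auditory dual-task walks.
- Modality effect: [(DTv + ST) − (DTa + ST)] / 2 = (DTv − DTa) / 2
- Complexity by modality: (DTv − ST) − (DTa − ST) = DTv − DTa

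ST cancels from both, and the second contrast is twice the first. Test statistics do not depend on scale, so the two tests are identical. A simulated example with 48 participants gave F = 8.009 for both; it illustrates the identity and estimates nothing about this study. Group comparisons of these two contrasts use the same per-participant score, so group by modality and group by complexity by modality also become one test. The complexity contrast, (DTv + DTa) / 2 − ST, is a different quantity and is not caught in this redundancy.

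**The case against.** The best defence is that the sentence was never meant for the ratio score. The formula stands in the Introduction, as a description of usual practice, and the Methods do not restate it. The Data Collection section treats cost as something read from the comparison of conditions, and the Trial Design section lists task condition as a factor. On that reading the dependent variable is raw performance, and task complexity is a legitimate factor. This would remove the first difficulty and makes the model correct for accuracy, response time and stimulus-locked EEG. It does not remove the second: raw gait still has three cells, and the primary outcome is worded around walking.

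A reader might also infer more than the documents support:
- *That the model fits no outcome.* Raw cognitive scores fill all four cells.
- *That one result will be reported as two.* This follows only if the single-task walk is copied into both modality cells, and no section plans that.
- *That the cost formula is wrong because it turns negative when a measure where higher is worse, such as response time or double support time, deteriorates.* Multiplying an outcome by −1 changes no F, p value or partial eta squared, so this is a matter of labelling.
- *That a linear mixed model is needed.* The defect lies in the factors, and ANOVA with the right factors would do.

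Finally, an article condenses, and an unseen analysis plan may separate the outcomes. But the article names the outcome, the factors and their levels, and these conflict with its own definition and list of conditions. That is a misstatement rather than an omitted detail.

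**Conclusion.** Wrong as written. For the gait dual-task cost the stated within-subject crossing has 2 of its 4 cells; for raw gait it has 3 of 4, and complexity by modality is not estimable. For raw cognitive outcomes and stimulus-locked EEG the stated factors are valid.

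The conclusion rests on the cost definition in the Introduction and on the single-task walk being one condition without stimuli, as its section describes. It depends on no assumed number. The size is structural: it says which terms can be tested, and it does not measure a bias in any estimate. The overall single-to-dual comparison and its interaction with group remain estimable for raw gait.

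**What to change.** Replace the single sentence under Statistical Analysis with three models:

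1. Dual-task cost: group (three levels) × modality (visual, auditory).
2. Raw gait: group × walking condition (single, dual-visual, dual-auditory).
3. Raw cognitive outcomes, and stimulus-locked EEG: group × task complexity × modality.

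Say which of the first two is the primary analysis for the gait cost, and settle this before the data are analysed. A sign convention for measures where higher is worse, and a mixed model in place of ANOVA, are optional.

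The cost is a few lines of text and the matching code. All the data that these models need are already planned.
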